### Auditing

5.19

No scheduled audits by the sponsor are intended. In case the competent authorities require on-site inspection or audit, the investigator must ensure the availability of all documents and support the work at any time.

### Ethics

5.20

The study will be conducted according to standard operating procedures (SOPs) meant to ensure that all parties involved abide by the principles of Good Clinical Practice (GCP)^[39,42]^ and the Declaration of Helsinki.^[43]^ Moreover, the Next GeneSiPS-Trial will be carried out in accordance with local statutory and implementing provisions.

### Approval of the institutional review board

5.21

Patients will not be enrolled until there is a positive vote from the institutional review board (IRB). The first IRB to approve the study design was the Ethics Committee of the Medical Faculty of Heidelberg (Trial Code No. S-605/2018).

### Protocol amendments

5.22

Changes to the protocol have to be made in writing and require the approval of all signatories of the protocol. Subsequent amendments also require a positive assessment from the competent IRB.

### Consent or assent

5.23

The study includes neonates, infants, and toddlers up to the age of <5 years who suffer from severe sepsis or septic shock during their inpatient stay in one of the participating study centers. A parent or legal guardian will be informed in detail about the background, content and objectives of the study in an informative discussion prior to enrollment in the study. Furthermore, the parents or legal representative will receive the information leaflet attached to this application. Written consent is required and documented by the signature of the parents or the legal representative on the declaration of consent. A child-friendly education is not suitable in this setting, as the children are very young and at the time of inclusion are severely impaired by the underlying disease. In addition, no specific cooperation by the children is required. Apart from the low blood loss, no harm to the children is foreseeable. In particular, no separate blood collection/puncture is required.

### Confidentiality

5.24

Data collected are handled in accordance with the provisions of the General Data Protection Regulation (GDPR) of the European Union and the European Council.^[44]^ All data containing the identity of the patients or control patients are only accessible to the attending doctors, nursing staff, and clinical monitor. For all other investigators involved in the study, the data are encrypted to a pseudonym. Likewise, only pseudonyms are used in publications. Only the investigators of the respective study site are able to assign pseudonyms to patient names. Decryption of the pseudonyms is only permitted in justified cases (e.g., important new findings with regard to the diagnosis and therapy of the underlying disease). Re-identification is also permitted if a patient wishes to assert their right to information or revocation.

## Discussion

6

In the 2016 International Guidelines for Management of Sepsis and Septic Shock (of adult patients), the Surviving Sepsis Campaign (SSC) states that “appropriate routine microbiologic cultures always include at least two sets of blood cultures (aerobic and anaerobic).” The reason for this is the fact that the first pair of blood cultures achieves only a sensitivity of about 70% regarding the identification of the causative pathogens of bloodstream infections.^[14,15]^ The second pair accomplishes a sensitivity of 80% to 90%, resulting in over 98% with the third pair.^[14,15]^ If one considers all septic patients (and not only those with bloodstream infections), the causative pathogen is only successfully identified in one-third of cases.^[45–47]^ Underlying reasons might be technical shortfalls in blood culture acquisition, locally limited foci, fastidious organisms, or very low rates of viable microorganisms in blood stream further reduced by the beginning of antibiotic treatment before sample acquisition.^[22,48]^ In children, these limitations are of particular importance as blood volumes are small. Therefore, the SSC “international guidelines for the management of septic shock and sepsis-associated organ dysfunction in children” recommends “obtaining blood cultures before initiating antimicrobial therapy” but only “in situations where this does not substantially delay antimicrobial administration,”^[8]^ as a delayed onset of anti-infective treatment increases organ dysfunction in pediatric sepsis.^[48,49]^ In this context, the SSC mentions the potential benefit of new molecular technologies including the restriction, that currently used sequencing systems are limited to a predefined set of detectable pathogens.^[8,50]^ A prominent example is the direct detection of the (deoxy)ribonucleic acid (DNA/RNA) sequences of pathogens by means of polymerase chain reaction (PCR). It is a highly sensitive and specific, culture-independent method for the targeted detection of a specific pathogen.^[28–30,51,52]^ In particular, it enables the detection of pathogens that are difficult to cultivate, such as atypical pneumonia pathogens, viruses, or fungi.^[28,51]^ A pathogen can potentially be detected even if it has already been killed or significantly reduced in number by the first administration of antimicrobial therapy.^[53,54]^ However, in this context, it is necessary to distinguish between pathogen-specific and so-called broad-spectrum or universal PCR methods. In the first case, the DNA of specific pathogens is identified by the use of specific primers, while in the second case, primers are used which bind to conserved sections of the genome of bacteria or fungi. These so-called eubacterial or pan-fungal PCRs allow a broader search approach, but are significantly less sensitive. Moreover, it is often only possible to identify the pathogen family rather than the specific species.

In contrast, NGS is able to overcome the aforementioned weaknesses of a PCR-based technique as it uses a data-driven approach without any idea of the suspected species. Therefore, no specific primer design is required and bacterial, fungal, and viral pathogens can be identified in a single assay. In a slightly modified variant, NGS is even able to correctly identify mutations of the ribonucleic acid (RNA) virus Sars-Cov-2.^[55]^ However, despite NGS becoming increasingly more important in clinical microbiology (e.g., for strain typing or microbiome studies), only sporadic reports of NGS-analyzed clinical specimens have been published to date.^[56–64]^ Moreover, in contrast to these cases, the approach used in the trial presented here also offers the possibility of quantifying the patients’ pathogen load. In addition, using the SIQ sore our approach is able to provide a statement regarding the clinical significance of the finding.^[18,20]^

The Next GeneSiPS-Trial presented here seeks to extend the results of the Next GeneSiS-Trial to newborns, infants, and toddlers up to the age of 5 years. Young children in these age groups could particularly benefit from NGS-based diagnostics, since it significantly increases the chance to correctly identify the causative pathogen, and reduces the required blood sample volume and thus reduces the stress placed on children at the same time. Moreover, as children are particularly susceptible to toxic side effects of anti-infective drugs NGS might help to decrease therapy-associated risks and side effects. Taken together, NGS has the potential to be a disruptive innovation that might replace the old gold standard of culture-based microbiological diagnostics in pediatric sepsis in the intermediate-term.

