
In order to overcome these challenges, we recently introduced the concept of an unbiased sequence analyses of circulating cell-free deoxyribonucleic acid (cfDNA) by next-generation sequencing (NGS) for sepsis diagnostics.^[18–20]^ Using a quantitative score (sepsis indicating quantifier [SIQ] score), this NGS-based approach enables clinicians on the one hand to identify the relevant infecting organisms and on the other to differentiate the sepsis-causing pathogen from potential microbial contaminants (e.g., coagulase-negative staphylococci). Therefore, this method has proven to be superior to state-of-the-art molecular approaches for the diagnosis of infecting organisms (such as polymerase chain reaction [PCR]-based methods for pathogen identification) in specimens of septic patients. In contrast to these conventional PCR-based diagnostic procedures, NGS is an open approach and therefore not limited to the identification of a predefined list of probable species.

As newborns, infants, and toddlers are particularly susceptible to the toxic side effects of anti-infective drugs due to immature detoxification systems, they could exceptionally benefit from this quicker, more sensitive diagnostic tool, needing only 1 mL of patient blood.

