### Description of analysis techniques

5.5

Standard-of-care microbiological analyses: microbiological testing of potential pathogens in the different specimens will be performed according to the usual standard operating procedures of the respective participating institution.

Here, we exemplify briefly the blood culture testing at Heidelberg University Hospital which has been described in detail elsewhere^[27]^:

After the sterile collection of 0.5 to 10 mL whole blood, it is injected into an aerobic (and if possible half of it in an anaerobic) blood culture bottle (BACTEC PLUS, BD Biosciences, Heidelberg, Germany). In cases in which it is not possible to collect a sufficient amount of blood, only one aerobic blood culture bottle is inoculated. The blood culture bottles are then incubated for at least 5 days (BACTEC, BD Biosciences). Positive cultures are analyzed using VITEK2 (Biomerieux, Nuertingen) or MALDI TOF (Bruker, Madison, WI) and then subjected to an automated resistance test (VITEK 2). Herpes simplex-1 (HSV-1) or cytomegalovirus (CMV) DNA from plasma or tracheal secretions is identified by means of a quantitative real-time (RT) PCR.^[28]^ Wound swabs, catheter tips, and stool samples are also cultured using standardized methods.^[29,30]^

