### Next-generation sequencing (NGS)

5.6

The NGS-based diagnostics in the plasma samples of the study patients is carried out as follows (subject to any further technical developments).^[20]^ After the aseptic removal of 2.7 mL EDTA blood, EDTA plasma is obtained immediately by centrifugation for 10 minutes at 2500 × *g*. The plasma is then pipetted into 0.5 mL Eppendorf or 1.5 mL DNA LoBind tubes. Then, 80 μL is pipetted into a separate 0.5 mL Eppendorf tube in order to later determine the concentration of the reactive metabolite methylglyoxal (MG) from this.^[31]^ The Eppendorf tubes are then stored at –80 °C until further processing. Sample processing should be completed no later than 2 hours after the blood sample has been taken. The sample is transported for further processing to the Fraunhofer Institute for Interfacial Engineering and Biotechnology (Fraunhofer IGB, [name]) on dry ice. Here, plasma will be centrifuged again for 10 minutes at 16,000 × *g* and 4 °C and nucleic acids will be isolated using the QIAsymphony DSP Circulating DNA Kit (Qiagen, Hilden, Germany). The isolated nucleic acids (=freely circulating DNA [cfDNA]) are then quantified using the Qubit dsDNA HS Assay Kit (Life Technologies, Carlsbad, CA). In addition, quality control is carried out using the HS NGS Fragment Analysis Kit using a Fragment Analyzer or FEMTO Pulse (Advanced Analytical Technologies Inc., Heidelberg, Germany). The so-called NGS libraries are made from 0.5 to 1 ng cfDNA using the Nextera XT Library Preparation Kit (Illumina, San Diego, CA) or NEXTflex Cell Free DNA-Seq Kit (Bioo Scientific, Austin, TX) and then sequenced on a HiSeq2500 (Illumina, San Diego, CA). In the next step, human cfDNA is identified using NextGenMap. Reads mapping to the human reference genome (hg19, minimum identity between read and reference genome of 80%) and reads with low complexity (consecutive stretches of di- and trinucleotides along the whole read sequence) are excluded from further analysis.^[32]^ Finally, reads are assigned to systematic classification using the RefSeq database (release version 68; comprising 35,749 bacterial and 4340 viral genomes complemented by 12 selected fungal genomes) using the Kraken Taxonomic Sequence Classification System (Center for Computational Biology, Johns Hopkins University, Baltimore, MD).^[33,34]^ To quantify the respective reads, read counts are normalized to the corresponding library size. Of note, *Xanthomonas* species are excluded from further analyzes as they are well-known contaminants.^[35]^

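### The assay reads only cell-free DNA against a finite database, while the comparator can take in routine findings the assay cannot detect, so agreement should be reported for all organisms and for in-scope organisms

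*Protocol article*

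**What the plan says.** **Breadth.** The Introduction contrasts the method with conventional PCR and states that "NGS is an open approach and therefore not limited to the identification of a predefined list of probable species". The Discussion repeats the contrast: "no specific primer design is required and bacterial, fungal, and viral pathogens can be identified in a single assay". The next sentence there adds: "In a slightly modified variant, NGS is even able to correctly identify mutations of the ribonucleic acid (RNA) virus Sars-Cov-2".

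**Assay.** Section 5.6 works on DNA. "The isolated nucleic acids (=freely circulating DNA [cfDNA]) are then quantified using the Qubit dsDNA HS Assay Kit", and "The so-called NGS libraries are made from 0.5 to 1 ng cfDNA". No RNA extraction or reverse transcription is described. Reads are classified against RefSeq release 68, "comprising 35,749 bacterial and 4340 viral genomes complemented by 12 selected fungal genomes". Xanthomonas is then removed: its "species are excluded from further analyzes as they are well-known contaminants". The section allows the method to change with technical progress. Section 5.7 defines the SIQ score per species and puts unassignable reads in a separate column for which no score is interpreted.

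**Comparator.** The Abstract and section 3 call it culture-based. Section 5.5 says that standard-of-care testing "will be performed according to the usual standard operating procedures of the respective participating institution"; its one-site example includes PCR for HSV-1 and CMV DNA. Section 5.10 takes routine findings from other materials, tracheal secretions among them, into the evaluation if they fall within 72 hours of the NGS sample. Section 5.4 gives the expert panel the same range of results.

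**Analysis.** Section 5.16 compares NGS with standard of care case by case, using the McNemar test and Cohen's kappa.

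**The concern.** The first objective is to measure how well NGS detects the relevant infecting organisms compared with standard diagnostics. Two different things can make NGS negative where standard care is positive. The assay may fail to pick up an organism it could in principle see, or the organism may lie outside what a DNA library and this database can return. Only the first says something about assay performance. The second depends on what each site chooses to test for, and the protocol leaves that to local procedures across 6 to 10 hospitals. Eligibility (Table 1) accepts any suspected or proven infection and is not restricted to bacterial disease.

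If the two kinds of miss share one discordant cell, agreement and kappa partly describe the sites' test panels. A reader could not tell a weak assay from a wide reference. The panel has a smaller version of the same problem: in a child with no routine finding, an expert who takes the assay to be open may read more into a negative NGS result than it can bear.

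**Working it through.** The protocol gives no sample-size, power or agreement calculation to reproduce; 150 children is a feasibility figure (section 5.11). The check is therefore a comparison of sections and a bounded illustration.

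**1. Can every routine finding receive an NGS call?**
- Analyte: cell-free DNA, so an RNA virus without a DNA stage contributes nothing to the library.
- Database: 35,749 + 4340 + 12 = 40,101 genomes. Shares are 35,749/40,101 = 89.1% bacterial, 4340/40,101 = 10.8% viral and 12/40,101 = 0.03% fungal.
- Score: SIQ is defined per species in the count matrix. An organism absent from the database cannot receive a score under its own name.

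Some findings are thus undetectable by construction, as the assay is described.

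**2. Can such a finding reach the comparison?** Under a purely culture-based reference, RNA viruses cannot enter, and only a cultured organism missing from the database (or the excluded genus) would. Under sections 5.5 and 5.10, site-specific results from other specimens count, and PCR is among the methods named. The route is open, although no section says that RNA-virus tests are used.

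**3. What would it do?** Let u be the share of standard-of-care positives that are out of scope. Even if the assay finds everything it can see, positive agreement cannot exceed 1 − u. The protocol gives no value for u, so 5%, 10% and 20% are assumptions. Two denominators come from its own background figures:
- 15 positives: blood cultures negative in more than 90% of children (Introduction), so at most about 10% of 150.
- 50 positives: a pathogen identified in one-third of septic patients (Discussion), one-third of 150.

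| Positives | Assumed u | Out-of-scope cases | Ceiling on agreement | Exact 95% CI |
|---|---|---|---|---|
| 15 | 5% | 1 | 14/15 = 93.3% | 68.1–99.8% |
| 15 | 10% | 2 | 13/15 = 86.7% | 59.5–98.3% |
| 15 | 20% | 3 | 12/15 = 80.0% | 51.9–95.7% |
| 50 | 5% | 2 | 48/50 = 96.0% | 86.3–99.5% |
| 50 | 10% | 5 | 45/50 = 90.0% | 78.2–96.7% |
| 50 | 20% | 10 | 40/50 = 80.0% | 66.3–90.0% |

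Cases are rounded to whole children. For 50 positives at 5%, 2.5 is taken as 2; with 3 the ceiling is 47/50 = 94%. At u = 0 the ceiling is 100% and the problem disappears.

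**4. Where does it land?** A child whose only routine finding is out of scope falls in one McNemar cell, standard-of-care positive and NGS negative. The distortion is one-sided and does not average out.

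**The case against.** A reader might infer that the protocol advertises a test for all bacteria, fungi and viruses and then contradicts itself. It does not say all. In both places the contrast is with primer-targeted PCR, the database holds members of all three classes, and the Discussion itself signals that the RNA-virus application used a modified method. The list is not strictly fixed either, since section 5.6 allows for technical change. What stands is that the Introduction's wording carries no qualifier and is wider than section 5.6.

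A reader might also infer that out-of-scope cases are scored as NGS failures or reported as having no pathogen. No section states such a rule. Organism-level handling may sit in the full protocol, an analysis plan or the adult-trial publication to which section 5.16 refers, so its absence from the article is not the point. The point is that the comparator is called culture-based in one place and is wider in others, with a direct effect on what the agreement figure means.

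The size may well be small. The only viral tests named target DNA viruses, and no clinically relevant fungus is shown to be missing from the 12, which are not listed. A reader might assume that 20% to 40% of positives are RNA-virus-only and, with an assumed 80% detection rate, arrive at agreement of 0.80 × 0.80 = 64% down to 0.80 × 0.60 = 48%. Neither assumption has a source in the protocol.

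The panel sees routine results alongside NGS, so a virus found routinely is not hidden from it. The study is non-interventional and the panel's review retrospective. Finally, for the question of clinical usefulness, a missed RNA virus is a genuine miss. That is correct, and it is why the all-organism figure must be kept.

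**Conclusion.** The point holds as a cheap improvement. The assay described in section 5.6 is narrower than the Introduction's wording, and the comparison can admit routine findings that it cannot detect by construction. Where that happens, structural misses and true misses are pooled. The size is unknown from the protocol: near nil with a purely culture-based reference, and a ceiling of 96% to 80% with 50 standard-of-care positives if 5% to 20% are out of scope. Those shares are assumed, and the one-third figure behind the 50 describes septic patients in general, not this paediatric cohort. No sample size, significance level or power figure is affected, and the study treats its P-values as descriptive.

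**What to change.** In section 5.16, before NGS results are opened, classify each standard-of-care organism as in scope (DNA-bearing, present in the database version used and not excluded from calling) or out of scope. Report agreement twice: for all organisms, as clinical coverage, and for in-scope organisms, as assay performance. Neither figure replaces the other. Record the database version against which scope was judged, because section 5.6 lets the method change.

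Add one line to the panel material saying that a negative NGS result does not exclude RNA viruses or organisms outside the database. Qualify the Introduction's statement to DNA-bearing organisms represented in the named database.

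The cost is one scope list, one extra tabulation and a narrower breadth claim. No change to the assay, sampling or sample size is needed.

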### Justification for the enrolment of participants not capable of giving consent

6.1

In the “Next-Generation Sequencing (NGS) diagnostics of bacteremia in sepsis” (Next-GeneSiS)-Trial (DRKS-ID: DRKS00011911), we sought to validate the NGS-SIQ diagnostic approach to identify the causative pathogen in adult patients with sepsis and septic shock. The study presented here is intended to transfer this evidence to preterm and term neonates, infants, and young children. This is only possible if patients <18 years of age are enrolled.

### Trial status

6.2

Protocol version: Version: 1.2 (December 11, 2020).

Patient and data recruitment will start in September 2021 in all study centers which have approval from their IRB. Further study centers will be added as soon the protocol has been approved by their IRB.

## Correction

Equation 3 was originally misprinted with a line between k and j which has since been removed.
